## Appendix I: Bleeding outcome definitions

**Acute clinically overt bleeding** is defined as new onset, visible bleeding, signs, and/or symptoms suggestive of bleeding with confirmatory imaging techniques which can detect the presence of blood (e.g. ultrasound, computed tomography, magnetic resonance imaging)

The definition of **major bleeding** is adapted from the International Society on Thrombosis and Hemostasis (ISTH) definition.

**Major bleeding** is defined as a bleeding event which is:

- Acute clinically overt bleeding accompanied by one or more of the following:
  - A decrease in hemoglobin (Hgb) of 2 g/dL or more
  - A transfusion of 2 or more units of packed red blood cells
  - Bleeding that occurs in at least one of the following critical sites:
    - Intracranial
    - Intra-spinal
    - Intraocular (within the corpus of the eye; thus, a conjunctival bleed is not an intraocular bleed)
    - Pericardial
    - Intra-articular
    - Intramuscular with compartment syndrome
    - Retroperitoneal.
- Bleeding that is fatal.

**Clinically relevant non-major bleeding event:** The definition of clinical relevant non-major bleeding will be acute or sub-acute clinically overt bleeding that does not satisfy the criteria for major bleeding and that leads to one or more of the following:

- 1) hospital admission for bleeding.
- 2) physician-guided medical or surgical treatment for bleeding.
- 3) a change in antithrombotic therapy.

**Minor bleeding events:** All acute clinically overt bleeding events not meeting the criteria for either major bleeding or clinically relevant non-major bleeding will be classified as minor bleeding.

**Fatal bleeding event** is defined as a bleeding event that the adjudication committee determines to be the primary cause of death or contributes directly to death.

All acute clinically overt bleeding events will be adjudicated as a major bleeding event, or clinically relevant non-major bleeding event. Minor bleeding events will not be adjudicated.

[http://www.nejm.org/doi/suppl/10.1056/NEJMoa1107039/suppl\\_file/nejmoa1107039\\_protocol.pdf](http://www.nejm.org/doi/suppl/10.1056/NEJMoa1107039/suppl_file/nejmoa1107039_protocol.pdf) Accessed July 31 2015.

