### **5.9 Proposed Frequency and Duration of Follow-up**

**Visit #1 (31-90 days after discharge):** All subjects will be assessed during follow-up at 31-90 days after discharge from their index cardiac surgery. Details of MACE and major bleeding events which occurred after hospital discharge will be recorded. As well, subjects' list of medications will be updated. Specifically, a detailed history of OAC use will be obtained, including the date of initiation, prescriber, dose, and type.

In this visit, subjects in the intervention group will return their data transmitters, have their wearable sensors removed (if still worn by the participant), and undergo a 12-lead ECG. Subjects in the control group will undergo a 12-lead ECG during this follow-up visit as well.

**Visit #2 ( $6\pm 1$  months after surgery):** Subjects will be assessed during a second follow-up visit at  $6\pm 1$  months after surgery. At this visit, all subjects will receive 14 days of continuous cardiac rhythm monitoring with a wearable adhesive cardiac monitoring device. All subjects will be educated on the proper use of the device. Details of MACE and bleeding events which occurred since the first follow-up visit will be recorded. As well, subjects' list of medications will be updated. A detailed history of OAC use will be obtained, including the date of initiation, prescriber, dose, type. At this visit, all subjects will undergo a 12-lead ECG.

**Visit #3 ( $9\pm 1$  months after surgery):** This visit will be conducted by telephone. At this visit, a history of OAC use will be obtained (type, dose, prescriber).

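### Visit 1 records only major bleeding and Appendix I gives its bleeding classes different onset wording, so in an open-label trial an early bleed can be classed before blinded review and under unclear rules

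*Supplement*

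**What the plan says.** **Outcome.** Protocol section 5.12 (outcome 9) is the proportion of subjects with major bleeding within 45 days of discharge, defined by Appendix I. SAP section 2.2.1 (outcome 9) keeps that window and adds one from day 46 to the last follow-up. Clinically relevant non-major bleeding appears in neither the secondary nor the descriptive list of the SAP.

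**Collection.** In protocol section 5.9, Visit 1 takes place 31 to 90 days after discharge, and "Details of MACE and major bleeding events which occurred after hospital discharge will be recorded". For Visit 2 the text is "Details of MACE and bleeding events which occurred since the first follow-up visit will be recorded".

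**Definition.** In Appendix I, acute clinically overt bleeding "is defined as new onset, visible bleeding, signs, and/or symptoms suggestive of bleeding with confirmatory imaging techniques", with no time limit. Major bleeding has two limbs. The first is "Acute clinically overt bleeding accompanied by one or more of the following", followed by a haemoglobin fall of 2 g/dL or more, "A transfusion of 2 or more units of packed red blood cells", or a critical site. The second is "Bleeding that is fatal", with no condition on onset. The clinically relevant non-major class is "acute or sub-acute clinically overt bleeding that does not satisfy the criteria for major bleeding" that leads to admission, treatment or a change in antithrombotic therapy.

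**Adjudication.** Appendix I says "All acute clinically overt bleeding events will be adjudicated as a major bleeding event, or clinically relevant non-major bleeding event", and its next sentence exempts minor bleeds. Section 5.3 has the committee, blinded to assignment, review reported bleeding without any limit on onset. Section 5.7 states that subjects and clinicians know the allocation.

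**The concern.** A blinded committee protects an outcome only if the events reach it. If the form for the first weeks asks only for major bleeds, someone at the site has to decide what is major, and that person knows who was monitored and probably who was anticoagulated. Section 5.13 expects that more AF detection may lead to more anticoagulant prescription, so bleeding is the natural harm to set against it, although the protocol does not describe the outcome in those words.

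The class definitions also overlap in an odd way: the milder class is open to a kind of onset that the wording of the non-fatal major class does not mention. Only the major class is analysed, so a bleed read into the milder class disappears from the bleeding comparison. With few events expected, one or two such readings would be visible in the result.

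**Working it through.** **Step 1: the plan's own figures.** No rate or sample size is given for bleeding. The trial is sized on AF/AFL detection, 3% against 10%, two-sided 5%, 80% power:

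n per arm = [1.96·√(2·0.065·0.935) + 0.8416·√(0.03·0.97 + 0.10·0.90)]² / 0.07² = 193.5, so 194. Then 194/0.98 = 197.96, so 198.

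Both agree with section 12.1, and neither depends on the bleeding definition.

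**Step 2: which collection rule covers the 45-day window.** Days up to Visit 1 fall under the narrow rule (major only). Later days fall under the Visit 2 rule (all bleeding).

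| Visit 1 on day | Days under the Visit 1 rule | Days under the Visit 2 rule |
|---|---|---|
| 31 | 31 of 45 (69%) | 14 of 45 (31%) |
| 38 | 38 of 45 (84%) | 7 of 45 (16%) |
| 45 to 90 | 45 of 45 (100%) | 0 |

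The rule for the same outcome therefore varies with the visit date. With Visit 1 on day 90, days 46 to 90 of the SAP's second window also come under the narrow rule. Visit 2 does not repair this, because it looks back only to Visit 1.

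**Step 3: one bleed, two readings.** Take a non-fatal, visible bleed that develops over two weeks and leads to a transfusion of two units.

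| | *Acute* read only through its definition | *Acute* read as the opposite of *sub-acute* |
|---|---|---|
| Major? | Yes: new onset, visible, two units | No: first limb not met, not fatal |
| Non-major? | Not applicable | Yes: sub-acute, treated by a physician |
| Named in the Appendix I adjudication sentence? | Yes | No |
| Covered by section 5.3? | Yes, if reported | Yes, if reported |
| In the bleeding outcome? | Yes | No |

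The first reading follows the definition. The second follows from the contrast that the appendix itself draws, since the added words in the non-major class would otherwise have little work to do. Nothing in the text decides between them.

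**Step 4: is there pre-sorting before the committee?** Minor bleeds are defined as acute overt bleeds that fit neither higher class, and they are not adjudicated. Someone must therefore call a bleed minor before it would go to the committee, although the preceding sentence sends all acute overt bleeds there. Together with the Visit 1 wording, this points to a decision at the site.

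**Step 5: size.** One uncounted subject moves an arm by 1/198 = 0.51 points. The rest is illustration on assumed rates. At a true rate of 2%, 198 × 0.02 = 3.96, about four subjects. Losing one in one arm only turns 4/198 = 2.02% into 3/198 = 1.52%, an apparent difference of 0.51 points between equal arms. If the same share is lost in both arms, the difference in points and the power (two-sided 5%, 198 per arm) become:

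| Share uncounted | Assumed 2% v 4% | Assumed 2% v 6% |
|---|---|---|
| 0% | 2.0; 21.3% | 4.0; 52.8% |
| 10% | 1.8; 19.6% | 3.6; 48.5% |
| 25% | 1.5; 17.0% | 3.0; 41.6% |
| 50% | 1.0; 12.7% | 2.0; 29.5% |

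If the true rates are equal, equal loss leaves a difference of zero.

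**The case against.** A reader might infer that only acute bleeds can be major, that only acute bleeds reach the committee, and that a transfused slower bleed is therefore lost to the trial. The documents do not support this.

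- Fatal bleeding is a separate limb without an onset condition.
- *Acute clinically overt* is a defined term. It rests on new onset and on visibility or imaging, not on speed, so a new visible gut bleed or an imaged pericardial collection can satisfy it.
- Section 5.3 places reported bleeding before the committee with no onset limit. The Appendix I sentence therefore conflicts with 5.3 and does not establish an exclusion.
- A bleed leading to admission is a serious adverse event under Appendix J, and hospitalisation or emergency visits are SAP outcome 10. Such an event stays in the data.

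It can also be said that Visit 1 is not the only source for the 45-day window, that the case report forms are not shown, and that nothing makes the site's label final.

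These points narrow the concern but do not remove it. Section 5.3 covers only bleeding that is reported, so it cannot recover a bleed that Visit 1 did not ask for. The documents do not say that adverse event or hospitalisation reports are passed to the committee, and neither route assigns a bleeding class. The undefined *sub-acute* remains, and two adjudicators could reasonably class the same bleed differently.

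**Conclusion.** The point holds as two inconsistencies that need to be reconciled. The firmer one is the Visit 1 wording: between 69% and 100% of the 45-day window is collected under a rule that in effect asks an unblinded site to decide what is major, and the rule changes with the visit date. That the site makes this call is an inference from the Visit 1 wording, the open-label design and the exemption of minor bleeds. The second is the onset wording in Appendix I, under which a non-fatal bleed meeting a major criterion could be classed as non-major and so leave the only analysed bleeding outcome. This is possible on the text, not certain.

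A reader might also infer that the monitoring strategy will look safer than it is. That does not follow: a site could under-report, or could report more readily in anticoagulated subjects. The direction is unknown. The only size that does not rest on an assumed rate or loss is about 0.5 points per uncounted subject. The issue concerns a secondary safety outcome and leaves the primary analysis and the sample size unaffected, but the correction is cheap enough to be worth making.

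**What to change.** 1. In section 5.9, have Visit 1 record all overt bleeding since discharge, as Visit 2 already does for its own interval, and let the blinded committee assign the class.
2. In Appendix I, use the same onset wording for the non-fatal major limb, the non-major class and the adjudication sentence. If *sub-acute* is kept, define it.
3. Reconcile the adjudication sentence with section 5.3, and state who may label a bleed minor and on what information.
4. For subjects whose Visit 1 has already passed, search the serious adverse event reports and the records behind SAP outcome 10 for bleeding, and send what is found to the committee. This recovers only events that reached those routes.

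The cost is a few more forms for a committee that already exists, and possibly a slightly higher count of major bleeds. No change to the sample size or the primary analysis is needed.

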## **Appendix J: Serious adverse outcome collection and reporting.**

### **ADVERSE EVENT REPORTING**

All Serious Adverse Events (SAEs) that occur following the subject's written consent to participate in the study through 30 days of discontinuation of dosing must be reported to reported to the study sponsor.

#### **Adverse Events**

- An Adverse Event [AE] is defined as any new untoward medical occurrence or worsening of a pre-existing medical condition in a patient or clinical investigation subject administered a medicinal product and that does not necessarily have a causal relationship with this treatment. An AE can therefore be any unfavorable and unintended sign (including an abnormal laboratory finding, for example), symptom, or disease temporally associated with the use of a medicinal product, whether or not considered related to the investigational product.
- The causal relationship to a medicinal product is determined by a physician and should be used to assess all adverse events (AEs). The causal relationship can be one of the following:
  - Related: There is a reasonable causal relationship between a medicinal product and the AE.
  - Not Related: There is not a reasonable causal relationship between a medicinal product and the AE.
- The term “reasonable causal relationship” means there is evidence to suggest a causal relationship.
- Adverse events can be spontaneously reported or elicited during open-ended questioning, examination, or evaluation of a subject. (In order to prevent reporting bias, subjects should not be questioned regarding the specific occurrence of one or more adverse events).

#### **Serious Adverse Events**

A **Serious Adverse Event (SAE)** is any untoward medical occurrence at any dose that:

- results in death
- is life-threatening (defined as an event in which the subject was at risk of death at the time of the event; it does not refer to an event which hypothetically might have caused death if it were more severe)
- requires inpatient hospitalization or causes prolongation of existing hospitalization (see **NOTE\***: below for exceptions)
- results in persistent or significant disability/incapacity
- is a congenital anomaly/birth defect
- is an important medical event, defined as a medical event that may not be immediately life-threatening or result in death or hospitalization but, based on appropriate medical and

scientific judgment, may jeopardize the subject or may require intervention (e.g., medical, surgical) to prevent one of the other serious outcomes listed above. Examples of such events include but are not limited to intensive treatment in an emergency department or at home for allergic bronchospasm; blood dyscrasias or convulsions that do not result in hospitalization.

Suspected transmission of an infectious agent (eg, pathogenic or non-pathogenic) via a medicinal product is an SAE.

Although pregnancy, overdose, adverse events of special interest, and cancer are not always serious by regulatory definition, these events must be handled as SAEs.

Any component of a study endpoint that is considered related to study therapy should be reported as an SAE (eg, death is an endpoint, if death occurred due to anaphylaxis, anaphylaxis must be reported).

**\*NOTE:** *The following hospitalizations are not considered SAEs:*

- A visit to the emergency room or other hospital department lasting less than 24 hours that does not result in admission (unless considered an “important medical event” or a life-threatening event)
- Elective surgery planned before signing consent
- Admissions as per protocol for a planned medical/surgical procedure
- Routine health assessment requiring admission for baseline/trending of health status (eg, routine colonoscopy)
- Medical/surgical admission other than remedying ill health state that was planned before study entry. Appropriate documentation is required in these cases
- Admission encountered for another life circumstance that carries no bearing on health status and requires no medical/surgical intervention (eg, lack of housing, economic inadequacy, caregiver respite, family circumstances, administrative reason)

### **Adverse Events of Special Interest**

In this study, the following adverse events are to be reported to BMS as serious events, regardless of whether these reports are classified as serious or unexpected:

Potential or suspected cases of liver injury including but not limited to liver test abnormalities, jaundice, hepatitis or cholestasis.

### **Serious Adverse Event Collecting and Reporting**

Following the subject’s written consent to participate in the study, all SAEs, whether related or not related to a medicinal product, must be collected, including those thought to be associated with protocol-specified procedures. SAEs must be recorded on CIOMS Form and reported to BMS within 3 business days to comply with regulatory requirements. A form should be completed for any event where doubt exists regarding its status of seriousness. Although overdose and cancer are not always serious by regulatory definition, these events should be recorded on a form and reported to BMS within 3 business days. All SAEs must be reported by confirmed facsimile (fax) transmission or reported via electronic mail to:

**SAE Email Address:** [contact]  
**SAE [contact]

If only limited information is initially available, follow-up reports may be required.

All SAEs must be collected that occur during the screening period and within 30 days of discontinuing dosing of a medicinal product. If applicable, SAEs must be collected that relate to any later protocol-specific procedure (such as follow-up skin biopsy).

The investigator should report any SAE occurring after these time periods that is believed to be related to a medicinal product or protocol-specified procedure.

An SAE report should be completed for any event where doubt exists regarding its status of seriousness.

If the investigator believes that an SAE is not related to a medicinal product, but is potentially related to the conditions of the study (such as withdrawal of previous therapy, or a complication of a study procedure), the relationship should be specified in the narrative section of the SAE Report Form.

SAEs, whether related or unrelated to a medicinal product, and pregnancies must be reported to the study sponsor within 1 business day. SAEs must be reported initially through the electronic case report form (eCRF); if necessary, the central coordinating centre will follow up to ask sites to record the SAEs on the CIOMS Report Form. Pregnancies will be reported on a Pregnancy Surveillance Form.

If only limited information is initially available, follow-up reports are required. (Note: Follow-up SAE reports should include the same investigator term(s) initially reported.)

If an ongoing SAE changes in its intensity or relationship to a medicinal product or if new information becomes available, a follow-up SAE report should be sent within 1 business day to the study sponsor (or designee) using the same procedure used for transmitting the initial SAE report.

All SAEs should be followed to resolution or stabilization.

### **SAE Reconciliation for SAEs related to BMS products**

The sponsor will reconcile the clinical database SAE cases transmitted to BMS Global Pharmacovigilance (GPV&E). Frequency of reconciliation will be done every three months and once prior to study database lock. BMS GPV&E will e-mail upon request from the sponsor, the GPV&E reconciliation report. Requests for reconciliation should be sent to [[contact]](mailto:[contact]). The data elements listed on the GPV&E reconciliation report will be used for case identification purposes. If the investigator determines a case was not transmitted to BMS GPV&E, the case will be sent immediately.

## **Health Authority Reporting (Worldwide)**

Investigators must adhere to local Health Authority Reporting Requirements and timelines. For studies conducted under a local health authority:

- Adverse drug reactions that are Serious, Unexpected, and at least Possibly Related to the drug (Suspected Unexpected Serious Adverse Reaction, SUSAR) and that have not previously been reported in the Investigators' Brochure, or reference safety information document will be reported promptly, within local reporting timelines, to the health authority in writing by the Investigator.
- A clear description of the suspected reaction should be provided along with an assessment as to whether the event is drug or disease related.
- The Investigator shall notify the health authority of any unexpected fatal or life threatening experience associated with the use of the drugs as soon as possible but no later than 7 calendar days after initial receipt of the information.

All SAEs should be reported to the study sponsor by entering the data into the SAE form of the eCRF. This will trigger an email notification to the coordination centre and sponsor. Site staff will also be required to print the SAE form and fax it to the Coordination Centre at [contact].

### **Unusual failure in efficacy**

Any unusual failure in efficacy of any BMS marketed drug product prescribed to the patient must be reported to the coordination centre within 1 business day of becoming aware of the event using a CIOMS form (<https://cioms.ch/wp-content/uploads/2017/05/cioms-form1.pdf>). The coordinating centre will report these events to BMS Pharmacovigilance within 2 business days of becoming aware to:

SAE Email Address: [[contact]](mailto:[contact])

SAE [contact]

To further define an unusual failure in efficacy: The underlying principle is that if a health product fails to produce the expected intended effect, there may be an adverse outcome for the patient, including an exacerbation of the condition for which the health product is being used. Clinical judgment should be exercised to determine if the problem reported is related to the product itself, rather than one of treatment selection or disease progression, since health products cannot be expected to be effective in 100% of the patients. One example of unusual failure in efficacy is a previously well-stabilized condition that deteriorates when the patient changes to a different brand or receives a new prescription. Another example of a case that should be reported on an expedited basis is a life-threatening infection where the failure in efficacy seems to be due to the development of a newly resistant strain of bacterium previously regarded as susceptible.

### **Non-Serious Adverse Events**

A nonserious adverse event is an AE not classified as serious.

## **Non-Serious Event Collecting and Reporting**

The collection of non-serious adverse event (NSAE) information should begin at initiation of a medicinal product. Nonserious adverse event information should also be collected from the start of a placebo lead-in period or other observational period intended to establish a baseline status for the subjects.

Nonserious AEs should be followed to resolution or stabilization, or reported as SAEs if they become serious. Follow-up is also required for nonserious AEs that cause interruption or discontinuation of a medicinal product, or those that are present at the end of study treatment as appropriate.

Nonserious Adverse Events related to any BMS product are provided to BMS via annual safety reports (if applicable), and interim or final study reports.

